**Fig. 1 Fig1:**
[figure not shown]
Diagnostic Algorithm. PCR and NS1 results are obtained from analyzing the enrolment sample while IgM and IgG results are obtained from analyzing an acute phase sample (S1) and a follow-up/early convalescent phase sample (S2). In the presence of a clinical syndrome that might be dengue, a positive result on any of the first 3 tests is sufficient for a diagnosis of “laboratory confirmed acute dengue”

### Data management

A customized data entry software tool was developed consisting of a Microsoft Access database with a graphical user interface which follows the layout of the paper CRFs. An import function for laboratory results is built into the data entry tool in order to facilitate automatic uploads at the sites where this is technically feasible. The laboratory section of the paper CRF as well as the data entry software tool was adapted to site-specific units in order to avoid conversion errors during data entry. The data entry software is installed on designated computers with restricted access. Entered data is stored locally at the site and can be edited until uploaded to a secure server at the coordinating centre in Heidelberg. Uploads are automatically integrated into the central database. The data of the central server is mirrored to a secure backup server.

Double data entry is carried out for 100 % of the first 100 patients enrolled at each site, then gradually reducing to a minimum of 5 % double data entry depending on the proportion of discrepancies between 1^st^ and 2^nd^ entries. Plausibility checks as well as range checks are built into the data entry tool, so that the data quality is checked in real time during data entry. Once the data is uploaded to the central server, the quality is checked again for plausibility and missing values by pre-programmed algorithms. The resulting query reports are relayed back to the local sites for correction before the data is again uploaded and processed for analysis.

Data and study materials will be stored for a minimum of 5 years at each site after the completion of the project. Individual SOPs will be written for continued storage or destruction according to local requirements and the availability of facilities for long-term storage. After analysis, the coordinating centre in Heidelberg will archive the database for long-term storage.

### Clinical monitoring

Independent monitoring has been integrated into the programme of work from the outset to ensure full compliance with Good Clinical Practice standards and all regulatory requirements. Monitoring teams from the OUCRU Clinical Trials Unit travel intermittently to all study sites in Southeast Asia, while a team from Heidelberg is responsible for the Latin American sites and Bangladesh. Following a site initiation visit, the first monitoring visit takes place after 50–100 participants have enrolled, followed by regular visits (at least annually) depending on recruitment rates. The monitors review study eligibility and informed consent for 100 % of the enrolled subjects. Data accuracy for all clinical information and all routine laboratory results (haematology and biochemistry) is also reviewed for 100 % of all participant CRFs during the first 6 months of enrolment at each site. Thereafter this percentage is maintained or decreased based on the error rate found during the most recent monitoring visit. At the end of each visit, the monitoring team meets with the site principal investigator and relevant study staff to review and present any findings, and on subsequent monitoring visits the teams review changes made in response to previous findings/recommendations.

### Statistical methods and analysis of results

The statistical methodology to be used for the primary objectives is summarised briefly in the following section. Detailed analysis plans will be formulated and documented prior to commencement of particular sections of the analysis relating to specific aims.

#### Sample size

We anticipate that dengue will be confirmed in ~ 50 % of the patients enrolled in Asia and ~ 20–30 % of the patients enrolled in Latin America. We also expect to make a definite negative diagnosis – i.e. that the patient did not have dengue – in at least 80 % of the remaining patients. Among hospitalised patients enrolled in previous descriptive studies in Vietnam around 5 % of cases progressed to severe disease; there is currently no data available for patients managed in the community but the progression rate is likely to be lower. In this study, among patients with confirmed dengue we will use two definitions of more severe disease: 1) severe dengue as defined in the new WHO 2009 classification scheme and 2) the combined endpoint of hospitalization or IV fluid administration or severe dengue. From a total enrolment of 7–8,000 cases we anticipate that around 3,000 dengue cases will be included in the cohort, potentially with 100–150 patients progressing to severe disease, primarily dengue shock syndrome. Hospitalization and/or IV fluid administration are likely to be considerably more common but will vary according to resources available and local clinical guidelines; however it seems plausible that the *relative* effect of risk factors on outcome will be similar across countries and regions. A dengue cohort of this size should allow for the assessment of up to 15 candidate risk factors even for the less frequent outcome of severe disease.

#### Development of a robust case definition for dengue

We will assess a broad range of clinical and laboratory parameters in order to develop a robust clinical case definition for dengue; covariates assessed will include demographic information, symptoms at presentation, examination findings, and readily available laboratory parameters such as the haematocrit, white blood cell count, lymphocyte count, platelet count etc. as well as simple biochemical measures such as AST, ALT, plasma albumin etc. Development of the diagnostic algorithm will follow standard recommendations for clinical prediction models [29]. Logistic regression will be the primary statistical model but we will also investigate modern flexible classification algorithms such as classification trees and random forests [30]. We anticipate that early changes in serial haematological markers, in particular the platelet count, white blood count and/or lymphocyte count may facilitate diagnosis. Therefore more complex models that include changes in marker values between successive days will also be investigated.

The presumptive case definition for dengue versus OFI may vary according to the background endemicity of other diseases, and we will investigate whether stratification by country or region is necessary. Potential heterogeneity will be assessed by including a fixed continent effect and random country/site effects (mixed effects model), and by testing for covariate-continent/country interactions (fixed effects model) in the logistic model [29].

The main aim for this section of the work is to develop a dengue case definition that can be reliably used at the primary healthcare level, but we may also be able to suggest modifications that could be incorporated into the algorithm if used at higher level healthcare facilities or in middle income countries with more resources available at the primary level. If appropriate the final model will be simplified to a point scoring system or electronic application for direct clinical use [31].

#### Prediction of risk for progression to severe dengue

Among patients with confirmed dengue we will identify simple clinical and laboratory parameters associated with either of the two definitions of more severe disease described above. Heterogeneity of outcomes will be assessed prior to pooling datasets from different countries. Classical prognostic models depend on baseline covariates only. However, we anticipate that early changes in serial haematological markers, in particular the platelet count, white blood count and/or lymphocyte count, or potentially in clinical parameters may carry important additional prognostic information. Thus there is a need to incorporate longitudinal data into the prognostic models and to update the models based on incoming data – e.g. by developing partly conditional models or joint models of longitudinal markers and outcome [32, 33].

#### Identification of early virological correlates of severe dengue

We will test the hypothesis that viral markers associated with development of severe dengue can be identified within the first 3 days of fever. We will define the sensitivity, specificity, positive and negative predictive values of NS1 detection within 3 days of fever onset for the same severity measures as indicated above and will also explore the use of statistical models for severity prediction.

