### Primary objectives

The study aims to improve diagnosis and clinical management of dengue through approaches designed a) to differentiate between dengue and other common febrile illness within 72 h of fever onset, and b) among patients with dengue to identify markers that are predictive of the likelihood of evolving to a more severe disease course.AIM 1: To identify clinical and/or simple laboratory parameters which differentiate between dengue and non-dengue illness within the first 72 h of fever, with the overall aim of developing a robust case definition for dengue.AIM 2: To identify clinical and/or simple laboratory parameters among dengue infected patients that predict likely progression to a more severe disease course.AIM 3: To identify virological correlates of severe dengue – in particular to assess plasma viremia and NS1 antigenemia within the first 72 h of fever in patients with confirmed dengue.AIM 4: To identify early serological correlates of severe dengue, in order to characterize differences between severe and uncomplicated disease.

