### Case definitions

Laboratory diagnosis of a dengue case will be in accordance with current WHO criteria [9]. The diagnostic algorithm is shown in Fig. 1. Briefly, any case with virological evidence of dengue as shown by a positive RT-PCR assay or NS1 ELISA test, or who has IgM seroconversion between paired specimens, is defined as having laboratory-confirmed dengue. A diagnosis of OFI is assigned to participants with no laboratory evidence of acute or recent dengue. Among participants with confirmed dengue a probable primary infection is defined by negative IgG Capture results on both the enrolment and follow-up samples, while a probable secondary infection is defined by a positive IgG Capture result in either or both the enrolment and follow-up samples.

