#### Diagnostic tests

This is a prospective observational study in which dengue diagnostic tests are performed on plasma samples from suspected dengue patients. The diagnostic tests are not performed in real time but batch tested at intervals; thus neither the patient nor the study/attending doctors are given the results of the tests as we intend to evaluate their accuracy in identifying patients who progress to severe dengue without the bias introduced by physicians interpreting and making clinical management decisions based on these test results. The routine diagnostic tests performed at each site are available to the treating clinicians as per the local standard of care. The research diagnostic tests are not routine in these settings and therefore we are not altering the current standard of care in the outpatient setting.

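### NS1 positivity alone can confirm dengue, so estimating NS1 accuracy for severity within confirmed dengue overstates sensitivity and understates specificity to the extent that NS1-negative dengue is missed

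*Protocol article*

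**What the plan says.** Four parts of the protocol article bear on this.

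- **Case definitions** and the **Fig. 1** legend set an either-or rule. Confirmation goes to "any case with virological evidence of dengue as shown by a positive RT-PCR assay or NS1 ELISA test", or to a patient "who has IgM seroconversion between paired specimens, is defined as having laboratory-confirmed dengue". The legend adds that "a positive result on any of the first 3 tests is sufficient for a diagnosis", and that "PCR and NS1 results are obtained from analyzing the enrolment sample".
- **Primary objectives**, Aim 3, is to "assess plasma viremia and NS1 antigenemia within the first 72 h of fever in patients with confirmed dengue".
- **Sample size** fixes the outcomes: "among patients with confirmed dengue we will use two definitions of more severe disease". These are the 2009 WHO severe category and a composite that adds admission and intravenous fluids.
- **Identification of early virological correlates of severe dengue** plans the "sensitivity, specificity, positive and negative predictive values of NS1 detection within 3 days of fever onset for the same severity measures", and also mentions exploratory prediction models.

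**Diagnostic tests** explains why the research results are withheld from clinicians: "we intend to evaluate their accuracy in identifying patients who progress to severe dengue" should not be disturbed by care decisions that respond to the tests.

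**The concern.** The marker under evaluation is also a ticket into the cohort in which it is evaluated, and both roles use the same enrolment sample. Every NS1-positive patient enters. An NS1-negative dengue patient enters only if another test succeeds. Any incomplete capture therefore thins the NS1-negative cells of the table and leaves the NS1-positive cells whole.

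Withholding results from clinicians does not help here: it stops the result from steering care, not from steering cohort membership. At stake is how NS1 would be described as an early severity marker under a primary aim: as detecting a larger share of severe cases, and clearing a smaller share of mild ones, than it does among all dengue patients.

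**Working it through.** **The plan's own figures.** The article gives no NS1 accuracy for severity, so there is no such figure to reproduce. The cohort size does reproduce: 40% confirmed (Exclusion of children under 5 years) times 7,000, 7,500 and 8,000 gives 2,800, 3,000 and 3,200, against a stated figure of around 3,000. The Timeline's 2510/5996 is 41.9%, stated as 42%.

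**Formulas.** Let s and n be the true probability of NS1 positivity in severe and non-severe dengue. Let c1 and c0 be the probability that PCR or IgM captures an NS1-negative severe or non-severe case. Let S and N be the numbers of severe and non-severe cases.

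- Observed sensitivity = s / (s + (1−s)c1), above s whenever c1 < 1.
- Observed specificity = (1−n)c0 / (n + (1−n)c0), below 1−n whenever c0 < 1.
- Observed odds ratio = true odds ratio × c0/c1, unchanged if c0 = c1.
- PPV = sS / (sS + nN), which contains neither c1 nor c0.
- Observed NPV = (1−n)c0N / ((1−n)c0N + (1−s)c1S), unchanged if c0 = c1.

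**Forward calculation.** Assumed: s = 0.75, n = 0.70, and all capture rates. S = 150 of 3,000 is the upper end of the article's expected number of severe cases. The true odds ratio is (0.75/0.25)/(0.70/0.30) = 1.29. For equal 90% capture, sensitivity = 0.75/(0.75 + 0.225) = 76.9% and specificity = 0.27/(0.70 + 0.27) = 27.8%.

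| Capture, severe / non-severe | Sensitivity | Specificity | Odds ratio | PPV | NPV |
|---|---|---|---|---|---|
| 100% / 100% | 75.0% | 30.0% | 1.29 | 5.3% | 95.8% |
| 90% / 90% | 76.9% | 27.8% | 1.29 | 5.3% | 95.8% |
| 95% / 90% | 75.9% | 27.8% | 1.22 | 5.3% | 95.6% |
| 95% / 80% | 75.9% | 25.5% | 1.08 | 5.3% | 95.0% |
| 95% / 70% | 75.9% | 23.1% | 0.95 | 5.3% | 94.4% |

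**Backward calculation.** Take a cohort as it would be seen: 3,000 confirmed, 150 severe, and an assumed 70% NS1 positive in both groups. The cells are 105 severe positive, 45 severe negative, 1,995 non-severe positive and 855 non-severe negative. Add M missed NS1-negative dengue patients to the negative cells only.

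| M and their severity rate | Sensitivity | Specificity | PPV | NPV |
|---|---|---|---|---|
| 0 | 70.0% | 30.0% | 5.0% | 95.0% |
| 100, same rate (5%) | 67.7% | 32.3% | 5.0% | 95.0% |
| 300, same rate | 63.6% | 36.4% | 5.0% | 95.0% |
| 300, double rate | 58.3% | 36.1% | 5.0% | 93.8% |
| 300, none severe | 70.0% | 36.7% | 5.0% | 96.3% |

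M is not in the article. The nearest bound comes from Sample size, which expects a definite negative in at least 80% of unconfirmed patients. Up to 20% of 4,000 to 5,000, or 800 to 1,000, could then be undetermined. On the December 2015 figures this is 20% of 5,996 − 2,510 = 3,486, or 697. How many of them have dengue is unknown.

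**The case against.** **The estimates are correct for the stated population.** The article names confirmed dengue as the population, and for that group the figures are what they claim to be. That is true, but membership of the group depends on the marker, so the figures do not carry over to dengue patients in general.

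**Details belong in the analysis plan.** The statistical section describes itself as a brief summary, and a formal plan is said to exist. Tables by confirmation route could well be there. However, the article itself states the case definition, the population and the accuracy measures, and the problem lies in their combination.

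**The bias may be small.** PCR is run on early plasma and paired IgM is added, so capture could be high; if it is complete, the bias is zero. With 100 to 150 severe cases, the 95% interval around a sensitivity of 75% is about ±8.5 to ±7 points, wider than the 1.9-point shift at equal 90% capture. This stands as a limit on the size.

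**A reader might infer that all four measures are biased and that the association could reverse.** The documents do not support this. PPV uses only NS1-positive patients, all of whom enter, and the Pathogenesis section describes NS1 as highly specific for dengue. The reversal in the last row of the forward table needs an assumed 95% against 70% capture and a weak true association; the same factor, 0.70/0.95 = 0.74, takes a true odds ratio of 2 only to 1.47. Nor is unequal loss established. Quick recovery does not in itself remove the second specimen, because Laboratory evaluation falls back on the final acute sample. Pathogenesis reports a link between viremia and severity but calls the data inconsistent. Equal loss should not be presumed either, since PCR capture depends on viremia and a patient already IgM positive at enrolment cannot seroconvert.

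**A cohort confirmed without NS1 is not a clean substitute.** It leaves the NS1-negative cells, and so NPV, exactly as they were. It restores sensitivity and specificity only if PCR or IgM detection is unrelated to NS1 within each severity group, which is doubtful when PCR and NS1 share a sample. It can also bias PPV: applying 95%/80% detection to the NS1-positives gives 106.9/(106.9 + 1,596) = 6.3% instead of 5.3%. This stands, and is why the restricted cohort should sit beside the full one and not replace it.

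**Conclusion.** The point holds for sensitivity and specificity. The article's rules let only NS1-negative dengue be lost, so any loss of severe cases raises sensitivity and any loss of non-severe cases lowers specificity. PPV is unaffected, given high NS1 specificity. NPV and the odds ratio move only if capture differs by severity, and the direction of any such difference cannot be told from the documents.

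The size is unknown. At 75%/70% positivity and equal 90% capture, the shift is 1.9 points of sensitivity and 2.2 of specificity. With 100 to 300 missed cases at equal severity rates it is about 2 to 6 points of each. Positivity, capture rates and the number missed are all assumptions. This calls for companion analyses; it does not invalidate the NS1 work under Aim 3.

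**What to change.** In the Aim 3 analysis:

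1. Report NS1 sensitivity, specificity and odds ratio in two cohorts side by side: all confirmed cases, and cases confirmed without using NS1 (PCR positive and/or IgM seroconversion).
2. Keep PPV from the all-confirmed cohort.
3. Tabulate, by severity, the cases confirmed by NS1 alone.
4. Add a sensitivity analysis that varies the dengue status of NS1-negative patients whose diagnosis is undetermined, and report the resulting range for sensitivity, specificity and NPV.
5. State that confirmation partly depends on NS1, so that readers know which population each estimate describes.

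The cost is analysis-plan wording and a few tables from data already collected, with no change to conduct or care. Precision falls in the restricted cohort by an amount that depends on the unknown number of NS1-only cases, and some bias remains if PCR or IgM detection correlates with NS1.

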#### Identification of early serological correlates of severe dengue

We will assess a variety of antibody responses (neutralizing and enhancing titers against the 4 dengue serotypes plus antibody titers against E, DIII, prM and NS1 of the 4 serotypes) in relation to clinical outcome, plasma viremia and NS1 antigenemia, and will develop a model of the serological responses seen in order to identify correlates of severe disease.

### Ethical considerations

This research project follows international standards for the ethical conduct of research involving human subjects. Ethical clearance has been obtained from the responsible institutional and national boards for each participating country (Table 1). Prior to commencing the study 3-day workshops were arranged in each country to provide a) general training in research ethics and ICH-GCP and b) specific training on the study protocol for all staff, as well as to allow development of locally appropriate SOPs for enrolment, daily follow-up, sample management etc. together with designated staff members. All staff involved in the study completed the relevant training before the study commenced at their site, and additional courses are being provided at intervals to ensure GCP training is maintained up to date.

#### Informed consent

Written informed consent is obtained from all patients or from the parent/guardian of children, as described above in the section on patient enrolment.

#### Confidentiality

Participants are assured that all information generated in this study will remain confidential. All data (including clinical, laboratory and genetic data) are stored in password-protected databases. Participants’ names are recorded at the time of enrolment to allow for their identification at follow-up visits, but identifiable information is linked to stored data or samples only by a protected Master List. This list is not shared outside the study staff at a unique hospital, and no identifying information is transferred between sites. All CRFs and samples are labelled with a study identification number only and stored in suitable secure locations. Only persons who have signed the locally appropriate data protection commitment form have access to the password-protected computer where entered data is stored. After conclusion of the project data will be removed from the computers and stored in a safe place.

#### Diagnostic tests

This is a prospective observational study in which dengue diagnostic tests are performed on plasma samples from suspected dengue patients. The diagnostic tests are not performed in real time but batch tested at intervals; thus neither the patient nor the study/attending doctors are given the results of the tests as we intend to evaluate their accuracy in identifying patients who progress to severe dengue without the bias introduced by physicians interpreting and making clinical management decisions based on these test results. The routine diagnostic tests performed at each site are available to the treating clinicians as per the local standard of care. The research diagnostic tests are not routine in these settings and therefore we are not altering the current standard of care in the outpatient setting.

